## Methods

### Participants

Seventy-five (*n* = 75) students will be voluntarily recruited from different universities in Rome, Italy. The sample size for this study was determined based on power analysis using G*Power 3.1.9.7 (Faul et al., 2007). We calculated that the minimum required sample size to detect an effect size of *f* = 0.25 using a mixed analysis of variance (ANOVA) including within-subject (3-time points) and between-subject (3 groups) effects with 95% power and at a two-sided 5% significance level was 54 participants (18 per treatment arm). However, attrition is a common problem that occurs in RCT: around 20% of participants withdraw before completing the study protocol (Mason, 1999). In conclusion, we plan to recruit approximately 75 participants (25 per treatment arm).

NoiBene will be advertised by word of mouth, mailing lists, and sharing fliers on various social networks (i.e., Facebook, Instagram). Students will be informed about the implementation of a group intervention to promote well-being and to prevent psychological distress. They will receive information about the program and about the specific goal of the intervention. The organization and the calendar of the meetings will also be presented. Since many university courses include credits achievable by practical activities (highly specialized workshops), all participants will receive an intervention completion certificate that they can use to achieve such credits.

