## Statistical Analysis

Data will be processed using SPSS (IBM) version 27. Descriptive analysis will be run for all the sociodemographic and academic variables, on data related to the satisfaction questionnaires and on SCL-90-R and MCMI-III scores. Chi-Square tests will be used to investigate differences between participants in the three conditions on baseline demographic variables and gender variables. With the same aim, a series of Student’s *t*-test will be run on age variable and on all baseline measures. If the test will provide significant *p*-values, effect sizes will be calculated considering Cohen’s d (small > 0.20, medium > 0.50, large > 0.80). If some variables will result significantly different between conditions, they will be included as covariant in the further analysis. A series of mixed models of analysis of variance (ANOVAs) will be run to investigate the efficacy of the intervention on the PWBI, WEMWBS, TAS-20, SIB, MPS, LOSC, RRS, PSWQ, and AAQ scores, as a function of the factor between CONDITION (NB-G vs. NB-WB vs. WLC) and the factor within TIME (Baseline vs. Post-Intervention vs. Follow-Up). The level of significance was set at *p* < 0.05. Effect sizes will be calculated using partial eta squared and it will be interpreted based on benchmarks suggested by Cohen (2013): *n*^2^ = 0.01, small effect size; *n*^2^ = 0.06, medium effect size; *n*^2^ = 0.14 large effect size. The *post hoc* analyses of significant interaction will be conducted using the Bonferroni *post hoc* test.

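### Covariates for the efficacy models are picked by baseline significance tests across randomised arms, so chance settles the model and precision is lost

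*Protocol article*

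**What the plan says.** The Statistical Analysis section of the protocol article sets out a sequence.

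- Categorical variables: "Chi-Square tests will be used to investigate differences between participants in the three conditions on baseline demographic variables and gender variables".
- Continuous variables: a series of Student's t-tests, with the same aim, "will be run on age variable and on all baseline measures". Cohen's d follows where a test is significant.
- Consequence: "If some variables will result significantly different between conditions, they will be included as covariant in the further analysis".

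The efficacy analysis is a mixed ANOVA for each of nine instruments, with "the factor between CONDITION (NB-G vs. NB-WB vs. WLC") and "the factor within TIME (Baseline vs. Post-Intervention vs. Follow-Up"). The threshold is p < 0.05. Bonferroni is mentioned only for post hoc tests after a significant interaction. No covariate is named in advance. The Procedure section says that participants are placed at random into the three conditions.

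**The concern.** Under randomisation every baseline difference is a chance difference, so its p-value does not show whether a variable needs adjustment. The rule admits a variable that happens to cross 0.05 even if it does not predict outcome. It leaves out a strong predictor that does not cross.

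The test named also does not fit the design. A Student's t-test compares two groups. The text does not say which pairs of the three arms are compared, whether the tests are corrected, or whether one significant pair is enough. Two analysts could follow the paragraph and fit different models.

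The rule can also select the baseline of the outcome under analysis. That score would then be a covariate while also being the first level of TIME in the dependent variable.

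At stake are whether the model for both primary outcomes is fixed before data are seen, and how much precision a trial of 75 students gives up.

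**Working it through.** **The plan's own figure.** The Participants section gives 54 as the minimum "to detect an effect size of *f* = 0.25", in a mixed ANOVA "including within-subject (3-time points) and between-subject (3 groups) effects with 95% power". For the group-by-time interaction, λ = f²·N·m/(1−ρ), with f = 0.25, N = 54 and m = 3. Assuming ρ = 0.5 and sphericity (neither is stated), λ = 0.0625 × 54 × 3 / 0.5 = 20.25. With df 4 and 102, power is 0.958, so 54 is reproduced. It does not depend on the covariate rule.

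**Inputs for the check.** From the article: 25 per arm, three arms, and ten continuous variables (age plus nine instruments; subscales would add more). Assumed: all three pairs tested uncorrected at 0.05, normal data, a correlation ρ between baseline and later score of 0.3 to 0.7, and a 0.6 SD effect in both active arms.

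**How often the rule fires by chance**

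- Simulated chance that at least one of three pairwise t-tests is significant: 0.123 per variable. With one three-arm test it is 0.05.
- Expected number of chance covariates: 10 × 0.123 ≈ 1.2.
- At least one of ten, independent: 1 − (1 − 0.123)^10 ≈ 0.73. Simulated with correlation 0.3: 0.66; with 0.5: 0.57.
- One three-arm test each, independent: 1 − 0.95^10 = 0.40.
- An outcome's own baseline is therefore not a covariate in about 88% of trials (95% with a three-arm test).
- Smallest pairwise difference that is significant: t(0.975; 48) × √(2/25) ≈ 0.57 SD. A true 0.5 SD difference is flagged only 41% of the time.

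**Precision.** With unit variance, the contrast variance factor is 2(1−ρ) for change from baseline and 1−ρ² for ANCOVA on own baseline. The ratio is (1+ρ)/2.

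| ρ | change | ANCOVA | ratio | reduction |
|---|---|---|---|---|
| 0.3 | 1.40 | 0.91 | 0.65 | 35% |
| 0.5 | 1.00 | 0.75 | 0.75 | 25% |
| 0.7 | 0.60 | 0.51 | 0.85 | 15% |

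**Error rate and power.** These come from a simulated three-arm F test at one post-baseline time point, 25 per arm. The gated rule uses ANCOVA if own baseline is flagged and the change score otherwise.

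| ρ | type I error, gated | power, change | power, gated | power, ANCOVA |
|---|---|---|---|---|
| 0.3 | 0.037 | 0.43 | 0.44 | 0.61 |
| 0.5 | 0.044 | 0.57 | 0.58 | 0.69 |
| 0.7 | 0.046 | 0.79 | 0.80 | 0.86 |

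ANCOVA gains 0.61 − 0.44 = 17, 0.69 − 0.58 = 11 and 0.86 − 0.80 = 6 points over the gated rule. A repeat gave 0.58/0.68/0.86 against 0.43/0.57/0.81, that is 15, 11 and 5 points.

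With the 0.6 SD effect, the change-score and ANCOVA verdicts at 0.05 disagree in 25%, 19% and 10% of trials at ρ = 0.3, 0.5 and 0.7.

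**The case against.** The strongest reply is that the rule does little damage in itself. A simulation of the full design (three arms, three times, ten baseline variables, all flagged variables added) gave type I error of 0.043/0.047/0.042 at ρ = 0.3/0.5/0.7. Power was 0.44/0.59/0.83 with the rule and 0.44/0.59/0.84 with no covariates. This stands: the power loss is measured against a better pre-specified analysis, not against leaving covariates out.

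Three stronger readings are tempting, and the article does not support them.

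- A reader might infer that baseline is left unadjusted. Baseline is a level of TIME in every model, so the CONDITION by TIME test already compares change from baseline. What is usually absent is the baseline score as a covariate.
- A reader might infer that false positives rise. Simulated type I error lies between 0.037 and 0.047, slightly below nominal.
- A reader might infer that the covariate set differs from outcome to outcome. The text sends flagged variables into the further analysis without limiting them to one outcome. Read literally, the same set enters every model.

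It is also fair that the pairs and the absence of correction are assumptions. The use of Cohen's d points to pairwise tests, but the article does not say so. The 73% is an upper figure for ten variables, because these distress and well-being scales will be correlated.

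None of this defends choosing covariates by significance. It is a stated rule, not a detail left to another document.

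**Conclusion.** The concern holds as a matter of pre-specification and efficiency, and should be fixed. Covariates are chosen by chance results, from a two-sample test whose use across three arms is undefined, so the efficacy model is not settled before the data are seen.

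At least one of ten continuous variables would be flagged by chance in roughly 57–73% of trials under uncorrected pairwise testing, and in about 40% with one three-arm test each on independent variables. Compared with adjusting for own baseline by design, the plan forgoes a 15–35% reduction in contrast variance. That is roughly 5 to 17 power points at the assumed 0.6 SD effect. These sizes rest on assumed correlations of 0.3–0.7, normal data and a single post-baseline comparison; the article gives no correlation.

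The double use of a flagged own-baseline score is a real incoherence, but little numerical harm from it is shown. Keeping three TIME levels with own baseline always a covariate gave type I error of 0.058/0.051/0.049. No bias or inflated error is shown, and the sample size of 54 is unaffected by the rule.

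**What to change.** In the Statistical Analysis section:

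1. Delete the baseline chi-square and t-tests and the sentence that turns significant differences into covariates. Describe baseline by arm with summary statistics only.
2. For each outcome, name its own baseline score in advance as a covariate, whatever the observed imbalance.
3. Limit TIME to post-intervention and follow-up, so that baseline is not used twice. Adding the covariate while keeping Baseline in TIME would make the double use universal.
4. Make the CONDITION effect and the CONDITION contrasts at each time point, Bonferroni-adjusted, the efficacy tests in place of the three-level interaction.

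The cost is wording. The post hoc sentence, now tied to a significant interaction, must be rewritten. The Participants section must describe a matching test behind the sample size, because its present description rests on three time points. No new data are needed, since every baseline score is already collected. The change should be made before outcome data are seen.

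### The three-visit mixed ANOVA, run as written, uses only students with all three assessments, and the expected 20% withdrawal could leave about 15 of 75 randomised out of every efficacy test

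*Protocol article*

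**What the plan says.** In the protocol article, the Statistical Analysis section gives a single efficacy method for both primary scales and the secondary scales: "A series of mixed models of analysis of variance (ANOVAs) will be run to investigate the efficacy of the intervention". The model crosses "the factor between CONDITION (NB-G vs. NB-WB vs. WLC" with "the factor within TIME (Baseline vs. Post-Intervention vs. Follow-Up". The software is named ("Data will be processed using SPSS (IBM) version 27") and so is the effect measure: "Effect sizes will be calculated using partial eta squared". Significant interactions are followed by Bonferroni post hoc tests.

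The Participants section sizes the trial for the same model, "using a mixed analysis of variance (ANOVA) including within-subject (3-time points) and between-subject (3 groups) effects". The requirement, "with 95% power and at a two-sided 5% significance level was 54 participants (18 per treatment arm" at f = 0.25, is raised to about 75 (25 per arm) because "around 20% of participants withdraw before completing the study protocol".

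The Procedure section places the last assessment 6 months after the intervention ends. The article states no analysis population and no handling of incomplete records.

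**The concern.** A classical repeated-measures ANOVA works on a complete set of scores per person. With three levels of TIME in one model, a student missing any one assessment is removed from the whole analysis. SPSS repeated-measures GLM does this by listwise deletion. A student with baseline and post-intervention scores who misses only the 6-month questionnaire is therefore also lost from the post-intervention comparison. The main hypothesis in Aim and Scope concerns levels after the intervention, so collected data bearing directly on it would go unused.

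Two things are at stake. Observed scores are discarded. And a comparison restricted to students who completed everything is no longer the comparison that randomisation set up. The arms differ in what they ask of students: six 4-hour in-person meetings, online modules with a Tutor, or a wait with a choice of treatment after the follow-up measurements. Unlike loss across arms is thus plausible, although the article neither asserts nor quantifies it.

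**Working it through.** **1. Which model is fixed.** The words *mixed models* alone could mean a linear mixed model. The label ANOVA, the within and between factors, partial eta squared and the mixed-ANOVA power calculation all point to the classical analysis.

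**2. The plan's own sample size.** Inputs from Participants: f = 0.25, k = 3 groups, m = 3 time points, 95% power, 5% level. Assumed, because the article does not give them: correlation between visits rho = 0.5 and sphericity (epsilon = 1). For the group-by-time interaction:

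- lambda = f² x N x m / (1 - rho) = 0.0625 x 54 x 3 / 0.5 = 20.25
- df1 = (k - 1)(m - 1) = 4; df2 = (N - k)(m - 1) = 51 x 2 = 102
- Power at N = 54 is 0.958; at N = 51 it is 0.946.

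The smallest number giving equal arms is 54, so the stated figure reproduces. It depends on rho: the same formula gives 72 at rho = 0.3 and 33 at rho = 0.7.

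**3. What the expected withdrawal does.**

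- Complete cases: 75 x 0.80 = 60, about 20 per arm. Left out: 75 - 60 = 15.
- Power with 60 complete cases (rho = 0.5): 0.975.
- Number needed to retain 54 after 20% loss: 54 / 0.80 = 67.5, so 68. Recruiting 75 tolerates 1 - 54/75 = 28% loss.

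On the plan's own terms the allowance covers power.

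**4. What it could do to the estimate.** The article has no figures for this. The results below are simulations under assumed mechanisms, with rho = 0.5 and all loss occurring before follow-up.

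| Assumed loss | Error in completers' difference in change |
|---|---|
| 20% in each arm, related to outcome in the same way | about 0 at post (0.003 SD or less at both visits where loss depends on change at post) |
| 20% in each arm; loss in NoiBene arms depends on poor change at post (logistic slope 0.5, 1.0, 1.5 per SD), random in WLC; true effect 0.5 SD | +0.10, +0.17, +0.23 SD at post; about +0.05 to +0.12 SD at follow-up |
| 30% vs 10%, loss depends on a low post score; no true effect | about 0.11 SD at post (0.21 SD in the post score itself); about 0 in change to follow-up |

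The size, and even the visit affected, is set by the assumed mechanism.

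**The case against.** The strongest reply is that the article never says incomplete records are deleted. The same ANOVA could be run on imputed data with all 75 students, and the analysis set and imputation are details that a condensed article commonly leaves to a fuller document. This stands to a degree. A reader might infer from the sample-size text that withdrawals are planned to be excluded, but that text only enlarges the sample because attrition is common, as trials using likelihood models also do. The 15 is therefore conditional on the 20% being realised and on no imputation. What remains is that the article names a method which, as written, cannot use partial records, and a better one is available in the same software. The point is about the method chosen, not about a missing sentence.

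A reader might also take the simulated 0.1 to 0.2 SD as the bias of this trial. The article does not support that. The figures need loss that differs across arms, in its rate or in its relation to outcome, and no arm-specific forecast is given. The article also describes features that favour retention in every arm: Tutor contact intended to limit drop-out, a completion certificate for all participants, and treatment offered to the waiting list once follow-up is done.

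The advantage of a likelihood model should not be oversold either. In the examples every lost student already has a post-intervention score, which is where such a model helps most. The article gives no timing of withdrawal. Students who leave during the course may have baseline data only, and for them the model adds little and still relies on missingness at random.

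Finally, a reader might infer a sphericity failure from the unequally spaced visits. Unequal spacing does not by itself violate sphericity, and SPSS prints corrections; nothing here rests on it.

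**Conclusion.** The concern holds in a limited form. The stated efficacy analysis uses only students with all three assessments unless data are imputed, and no imputation is stated. At the plan's own 20% withdrawal, about 15 of 75 randomised students could be absent from every efficacy test, some of them with post-intervention scores in hand.

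This is not a finding of low power: about 60 completers exceed the 54 required (0.975 at assumed rho = 0.5), although the 54 itself rests on an unstated correlation. Nor is it a finding of a known bias. Bias is about zero if the rate of loss and its relation to outcome are the same in all arms, and about 0.1 to 0.2 SD at post-intervention under the assumed asymmetric mechanisms. Which applies cannot be told from the article. Because this is the only efficacy analysis named for both primary outcomes and the remedy is cheap, it should be changed before the data are analysed.

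**What to change.** Make the primary analysis a likelihood-based linear mixed model for repeated measures (SPSS MIXED, REML, unstructured covariance, small-sample degrees of freedom), with participants analysed as randomised. State one of two forms:

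- **(a)** Baseline, post-intervention and follow-up scores are all outcomes, with CONDITION, TIME and CONDITION x TIME and no baseline covariate. This keeps everyone with any assessment.
- **(b)** Post-intervention and follow-up scores are the outcomes, with the baseline score as covariate. This keeps everyone with at least one post-baseline score.

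The two should not be combined, because baseline would then be both an outcome and a covariate. Keep the complete-case ANOVA as a sensitivity analysis.

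Cost: slightly more analysis work, with the same data and software. Partial eta squared gives way to estimated mean differences with confidence intervals. The result relies on missingness at random, which should be stated.

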
### Aim and Scope

The purpose of this paper is to present the research protocol and recruitment process that will be employed for a randomized controlled trial (RCT) to evaluate the efficacy of NoiBene as a group intervention (NB-G). This condition will be compared with two other conditions: NoiBene as a guided web-based intervention (NB-WB) and with a waiting list condition (WLC). We hypothesized that participants in the NoiBene conditions (both NB-G and NB-WB), compared with participants in the WLC, would show after the intervention higher levels of mental health and well-being (Cuijpers et al., 2021) as well as an increase in academic performance and satisfaction (Bean and Eaton, 2001). We also predict that students in the NoiBene conditions will increase their emotional awareness and assertiveness, and they will reduce the level of perfectionism, repetitive thinking, and experiential avoidance (Di Consiglio et al., 2021a). However, we hypothesized that the NB-G conditions will be more effective than the NB-WB in improving assertiveness, since the group context guarantees more supervised practice (Salas and Cannon-Bowers, 2001; Gresham, 2002; Taylor et al., 2005), and it ensures a positive environment where the member can interact in an adaptive manner (Yalom, 1985). However, besides treatment efficacy, we expect that students can benefit from the NB-G or NB-WB differently based on their specific behavioral and motivational patterns. For example, bases on specific personality traits or set of values students could be more motivated to participate and benefit more from a guided web-based intervention or from a group intervention.

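### Efficacy is judged by a gated 3 × 3 interaction with baseline as a time level; baseline-adjusted planned contrasts would fit the stated hypotheses and be more efficient

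*Protocol article*

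**What the plan says.** **Hypotheses (Aim and Scope).** Participants in both NoiBene arms, "compared with participants in the WLC, would show after the intervention higher levels of mental health and well-being". For assertiveness, the group arm (NB-G) is expected to do better than the web arm (NB-WB). No time point is given for that second hypothesis.

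**Analysis (Statistical Analysis).** Each scale gets a mixed ANOVA with three conditions between subjects and "the factor within TIME (Baseline vs. Post-Intervention vs. Follow-Up" within subjects. Pairwise comparisons enter only as a follow-on step: the post hoc "analyses of significant interaction will be conducted using the Bonferroni" test. A variable becomes a covariate only if a baseline test shows a significant difference between conditions. No contrast and no decisive time point is named.

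**Sample size (Participants).** The calculation rests on a mixed ANOVA "including within-subject (3-time points) and between-subject (3 groups) effects". What it gives is described as the "minimum required sample size to detect an effect size of *f* = 0.25". The article reports that this number, "with 95% power and at a two-sided 5% significance level was 54 participants (18 per treatment arm", was then raised for attrition. Because "around 20% of participants withdraw before completing the study protocol", the authors write that "we plan to recruit approximately 75 participants (25 per treatment arm" being the target.

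**The concern.** The trial's questions are pairwise and, for the primary outcomes, tied to the end of the intervention. The planned test asks something broader: whether the three arms have different profiles over three occasions. Three consequences follow.

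- A significant interaction does not by itself confirm either hypothesis. It can come from a change between post-intervention and follow-up, or from a chance imbalance at baseline.
- A non-significant interaction closes the route to the comparisons the trial was set up to make.
- Randomised arms have the same expected baseline. Using baseline as an outcome level, rather than as a covariate in every analysis, gives up precision. The conditional covariate rule could also enter a score as a covariate while the same score remains a level of TIME.

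At stake is power that the trial could have from data it already plans to collect.

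**Working it through.** **1. Reproducing the plan's own figure.** The article gives neither the correlation between time points (rho) nor a sphericity correction. Assume rho = 0.5 and sphericity. The interaction has (3−1)(3−1) = 4 numerator df and 2(N−3) denominator df, with noncentrality λ = f²·N·3/(1−rho).

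- N = 54: λ = 0.0625 × 54 × 3/0.5 = 20.25, df 4 and 102, power 0.958.
- N = 51: λ = 19.125, power 0.946.

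So 54 is the smallest multiple of three that reaches 95%. At the same rho the TIME main effect would need 45 and the CONDITION main effect 168. The trial was therefore evidently sized on the 4-df interaction.

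**2. What f = 0.25 means here.** Suppose both NoiBene arms gain d SD over the waiting list at post-intervention and hold it. The centred group pattern is (1/3, 1/3, −2/3), with mean square 2/9. The time pattern (0, 1, 1) also has mean square 2/9. Hence f = (2/9)d, and f = 0.25 corresponds to d = 0.25 × 9/2 = 1.125 SD. The article's own benchmark for a large d is 0.80.

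**3. A smaller effect.** Take 25 × 0.8 = 20 evaluable per arm (N = 60) and d = 0.7. Then f = 0.156 and, at rho = 0.5, λ = 0.0242 × 60 × 3/0.5 = 8.71. With df 4 and 114 the omnibus power is 0.626.

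**4. The whole route, compared with planned contrasts.** By simulation under the same pattern, the gated route requires a significant interaction and then NB-G versus waiting list at post-intervention, at 0.05/3. The article does not say whether the post hoc test uses raw post scores or changes, so both are shown. The alternative is ANCOVA on the baseline score, with Holm adjustment over the two comparisons with the waiting list and no gate.

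| rho | Omnibus significant | Gated, raw post scores | Gated, change scores | Holm ANCOVA |
|---|---|---|---|---|
| 0.3 | 47% | 24% | 26% | 57% |
| 0.5 | 63% | 29% | 37% | 65% |
| 0.7 | 86% | 37% | 64% | 82% |

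The gap runs from 82 − 64 = 18 points to 82 − 37 = 45 points.

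**5. Where the gap comes from (rho = 0.5).** The variance factor is 1 for raw post scores, 2(1−rho) = 1 for changes and 1−rho² = 0.75 for ANCOVA. Ungated power for 20 versus 20 at 0.05/3 is about 40% for raw or change scores and 53% for ANCOVA. Starting from change scores, the steps are:

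- removing the gate: 37% to 40%;
- adjusting for baseline: 40% to 53%;
- testing two planned comparisons with Holm instead of three with Bonferroni: 53% to 65%.

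On raw scores the gate alone costs about 11 points (40% to 29%).

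**6. Assertiveness.** With assumed gains of 0.8 SD (NB-G) and 0.4 SD (NB-WB), rho = 0.5 and 20 per arm, the gated comparison of the two arms succeeds in about 9–12% of trials. A planned baseline-adjusted contrast at 0.05 succeeds in about 30%.

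**The case against.** An omnibus test followed by Bonferroni comparisons is conventional and valid, and it agrees with the way the trial was sized. At f = 0.25 it has 96% power with 54 participants and about 97.5% with 60. All of this stands, so preferring ANCOVA is a matter of efficiency and fit, not correction of an invalid test. The size of the gain also rests on rho, on the effect pattern and on the form of the post hoc test, none of which the article states.

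Stronger readings are tempting, but the document does not support them.

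- *The plan never answers its own question.* Bonferroni comparisons among three conditions include all three pairs of interest. What is missing is their status as planned, ungated tests at a named time.
- *Every comparison is a change-score comparison.* The interaction concerns change, but the form of the post hoc test is not given.
- *A difference between the two NoiBene arms at follow-up supports no hypothesis.* On the assertiveness scale (SIB), a difference in favour of NB-G would support one, since no time point is attached to it.
- *The gain is 63% against 83%.* The 83% belongs to a contrast of both NoiBene arms pooled against the waiting list. The hypotheses concern each arm, so that is not the contrast recommended here. Setting an unadjusted 70% for one arm against 40% at 0.05/3 would likewise mix significance levels; at 0.05/3 throughout it is 53% against 40%.
- *A test that is not directional is a defect.* The article specifies two-sided testing, and the fix keeps it.

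**Conclusion.** The point holds as one of efficiency and fit. The planned ANOVA is valid and is adequately powered for the effect it assumes. It is less efficient than baseline-adjusted planned contrasts at smaller effects, and a significant interaction is not in itself evidence for either hypothesis.

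For a 0.7 SD benefit in both NoiBene arms, held at follow-up, with 20 evaluable per arm, the chance of finding NB-G better than the waiting list at post-intervention rises from 24–26% to 57% (rho 0.3), from 29–37% to 65% (rho 0.5) and from 37–64% to 82% (rho 0.7). The direction is the same throughout this range; the size is not settled by the document. Part of the gain comes from limiting the primary family to two comparisons, not from baseline adjustment alone. The planned assertiveness contrast gains too, but remains weakly powered at the assumed 0.4 SD difference between arms.

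**What to change.** - Make the primary analysis of the two well-being scales (PGWBI and WEMWBS) a baseline-adjusted comparison at post-intervention. Use ANCOVA, or a repeated-measures model with the baseline score as covariate and post-intervention and follow-up as outcomes.
- Adjust for the baseline score always, whatever the baseline tests show, and drop baseline as a level of TIME.
- Pre-specify NB-G versus waiting list and NB-WB versus waiting list, Holm-adjusted, and NB-G versus NB-WB on the SIB as the key secondary contrast.
- Report each contrast with its estimate and 95% confidence interval regardless of any omnibus result. Treat follow-up contrasts as secondary.
- State in the Participants section that the sample size was based on the omnibus interaction.

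The cost is rewording of the analysis section and one sentence on sample size. No new data or participants are needed, and the named software (SPSS 27) can fit these models.

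### Partial eta squared is biased upward at the planned size: most no-effect interactions reach the small benchmark, and no significant interaction can be labelled small

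*Protocol article*

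**What the plan says.** The Statistical Analysis section plans a mixed ANOVA for each scale, with a between factor "CONDITION (NB-G vs. NB-WB vs. WLC") and a within factor "TIME (Baseline vs. Post-Intervention vs. Follow-Up"). Results are tested at 5% ("The level of significance was set at" p < 0.05). On size of effect it says: "Effect sizes will be calculated using partial eta squared and it will be interpreted based on benchmarks suggested by Cohen (2013"). The lowest benchmark is given as "0.01, small effect size", the middle one is 0.06, and the highest is "0.14 large effect size". Significant interactions then go to Bonferroni post hoc tests. The section mentions neither a bias-corrected index nor an interval for the effect size.

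The Participants section gives the sizes that matter. The minimum for the "effects with 95% power and at a two-sided 5% significance level was 54 participants (18 per treatment arm"), about 20% withdrawal is expected, and "we plan to recruit approximately 75 participants (25 per treatment arm").

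**The concern.** Sample partial eta squared cannot be negative, so with several numerator degrees of freedom and a modest sample it is well above zero even when nothing is happening. Fixed benchmarks take no account of this. The interaction is the term that carries the treatment effect, and it has 4 numerator degrees of freedom. If its typical null value already exceeds 0.01, the small label does not distinguish a weak effect from none. If the value needed for significance exceeds 0.06, every significant scale is described as medium or large even when the true effect is small. Readers would take these labels as the size of NoiBene's benefit, on both primary scales as well as the secondary ones.

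**Working it through.** **Inputs.** From Statistical Analysis: 3 conditions, 3 times, alpha 0.05, cut-offs 0.01, 0.06 and 0.14. From Participants: N = 54 (minimum) and 75 (recruited). With 20% withdrawal, 75 × 0.80 = 60. Interaction degrees of freedom: df1 = (3 − 1)(3 − 1) = 4 and df2 = 2(N − 3), that is 102, 114 and 144.

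**The plan's own figure.** For the within-between interaction, with f = 0.25 and an assumed correlation between times of 0.5 (not stated in the article), λ = f² × N × 3/(1 − 0.5). At N = 54 this is 0.0625 × 54 × 3/0.5 = 20.25, and power is 0.958. At N = 51 power is 0.946. So 54 is reproduced, which confirms that the sample size was set on the interaction.

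**No treatment effect.** Under normality and sphericity, partial eta squared follows Beta(2, N − 3). Hence:
- mean = 4/(4 + df2)
- P(at least c) = (1 − c)^(N − 3) × [1 + (N − 3)c]

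Example at N = 60 and c = 0.01: 0.99^57 × 1.57 = 0.5639 × 1.57 = 0.885.

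**Smallest significant value.** This is 4F/(4F + df2), with F the 5% critical value. At N = 60: 4 × 2.451/(4 × 2.451 + 114) = 9.804/123.804 = 0.079.

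| N | df2 | Null mean | P(≥ 0.01) | P(≥ 0.06) | P(≥ 0.14) | Critical F | Smallest significant value |
|---|---|---|---|---|---|---|---|
| 54 | 102 | 0.038 | 90.4% | 17.3% | 0.37% | 2.461 | 0.088 |
| 60 | 114 | 0.034 | 88.5% | 13.0% | 0.17% | 2.451 | 0.079 |
| 75 | 144 | 0.027 | 83.4% | 6.2% | 0.02% | 2.435 | 0.063 |

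Simulating 20,000 null data sets at each N gave 90.4%, 88.1% and 83.4% for the 0.01 cut-off. With equal arms, the smallest significant value is still 0.061 at N = 78 and first falls below 0.06 at N = 81 (0.059).

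**With a true effect** (noncentral F, λ = 2N × η²/(1 − η²)). Partial epsilon squared is 1 − (1 − η²)(df2 + 4)/df2. Mean sample values at N = 60:

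| True value | Partial eta squared | Partial epsilon squared |
|---|---|---|
| 0.01 | 0.044 | 0.010 |
| 0.06 | 0.092 | 0.060 |
| 0.14 | 0.169 | 0.140 |

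With a true value of 0.01 at N = 60, 24% of trials give 0.06 or more, and the significant ones average 0.10.

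**Do the upper cut-offs separate?** Yes. Over N = 54 to 75, 0.14 is reached in 66–68% of trials when the true value is 0.14, against at most 0.4% with no effect. The 0.06 cut-off is reached in 71–75% when the true value is 0.06, against 6–17% with no effect.

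**With the corrected index.** P(at least 0.01 with no effect) falls to 28.8%, 27.5% and 24.6% at N = 54, 60 and 75. The smallest significant value becomes 0.052, 0.047 and 0.037, so a significant interaction could be labelled small.

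**The case against.** Partial eta squared with these benchmarks is conventional, fits the planned ANOVA and is quoted without internal contradiction. The labels only describe: no test, error rate or sample size depends on them. Bonferroni post hoc tests are planned to show which arms differ, so the omnibus index need not show direction. All of this stands, and it limits the point to how size is reported.

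Three stronger readings are tempting, and the documents do not support them.

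- *The benchmarks cannot discriminate at this sample size, or reflect sample size more than effect.* The upper two cut-offs separate clearly, as shown in the working. Only the boundary between none and small fails.
- *The labels are the criterion of efficacy.* The stated criterion is p < 0.05.
- *Ineffective scales will be reported as small effects.* The article does not say that non-significant ANOVA results will be labelled. In the same section, Cohen's d for baseline comparisons is calculated only after a significant test. The ANOVA sentence carries no such condition, so the text leaves the matter open. If labels were confined to significant results, about 5% of null interactions would receive one, not 83–90%.

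A further objection is that correction does not cure selection on significance. That is right: at N = 60 with a true value of 0.01, significant partial epsilon squared still averages 0.07.

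One might also say that an article leaves reporting detail to a fuller plan. Here, however, the article names the index and the benchmarks, so the point concerns a stated method and not an omission.

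**Conclusion.** The point holds as a bias in the reported size of effect. For the CONDITION by TIME interaction at N = 54 to 75, the index averages 0.038 to 0.027 with no effect, roughly three to four times the small cut-off. Between 90% and 83% of null results reach that cut-off, and no significant interaction can fall below 0.063.

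The figures rest on normal outcomes, complete data at all three times, sphericity and no covariates. If sphericity fails with epsilon 0.75, about 78–86% of null results reach 0.01 and the smallest significant value is 0.070–0.097, so both conclusions survive. They do not carry over unchanged to the main effects. With no effect, TIME reaches 0.01 in 49–60% of trials and CONDITION in 70–77%, and a significant TIME effect can lie below 0.06 (smallest significant value 0.041–0.057).

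This is a minor but worthwhile correction to reporting. It does not threaten the trial's tests.

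**What to change.** Replace the effect-size sentence in Statistical Analysis so that it says three things:

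1. The omnibus effect size is partial epsilon squared or partial omega squared, with a confidence interval, in place of partial eta squared.
2. No size label is attached to a non-significant result.
3. Benefit is described by the differences NB-G vs WLC, NB-WB vs WLC and NB-G vs NB-WB at post-intervention and at 6 months, each with a 95% confidence interval. Size is judged from the interval, not from a label on the point estimate.

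The cost is a short change of text. The corrected index needs only F and its degrees of freedom, and no extra data or participants are required. The drawbacks are that reported values will look smaller and will be less directly comparable with papers that use partial eta squared. Results picked out because they are significant will still be inflated, which is why the interval should carry the interpretation.
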